## Discussion

3

To the best of our knowledge, this study protocol will be the first to investigate the effects of eccentric training on the structural and mechanical properties of PF in stroke survivors compared to conventional therapy. We hypothesize that a notable distinction will emerge between the two interventions, with the protocol incorporating eccentric strengthening demonstrating favorable outcomes. Moreover, the enhancement in gait speed and ROM will be associated with an improvement in passive and active PF stiffness.

The conceptualized program for this study aims to provide high-intensity training for individuals in sub-acute phase to effectively stimulate various forms of plasticity. The speed, load, and number of repetitions are the factors that form the basis of the eccentric work and upon which its relevance depends. Therefore, these parameters will be considered to achieve the targeted objective. In this context, a recent study conducted by Le Sant et al. (24) has presented compelling evidence that ET significantly enhances motor performance, particularly in terms of maximal strength and power, among individuals within neurological populations. This finding aligns with the observations of Clark and Patten (28) suggesting that the remarkable strength improvements attributed to eccentric training post-stroke may be linked to heightened quadriceps stretch reflex activity. This increased reflex activity supplements the voluntary neural drive during eccentric knee flexion contractions. Conversely, when considering the structural properties of the paretic muscle, (41) calculated the minimum detectable change for the thickness parameter, estimating it to be at 3 mm. Remarkably, these authors observed a noteworthy increase of 3 mm in the thickness of the SOL muscle following a 23-session eccentric training program focused on the PF, but this research was conducted with healthy individuals.

The conceptualized program for this study aims to provide high-intensity training for individuals in the sub-acute phase to effectively stimulate various forms of plasticity. The key factors—speed, load, and number of repetitions—form the basis of eccentric work and are critical to its efficacy. Therefore, these factors will be meticulously considered to achieve the targeted objectives. In this context, a recent systematic review by Le Sant et al. (24) presents compelling evidence that ET could significantly enhance motor performance, particularly in terms of maximal strength and power, among individuals with neurological diseases. The remarkable strength improvements attributed to ET post-stroke may be linked to heightened stretch reflex activity (28). Increased reflex activity may supplement the voluntary neural drive during eccentric contractions. Furthermore, regarding the structural properties of the paretic muscle, Geremia et al. (41) observed noteworthy increases of fascicle lengths (GM: 13.2%; GL: 8.8%; SOL: 21%) and muscle thickness (GM: 14.9%; GL: 15.3%; SOL: 19.1%) following 12 weeks ET focused on the PF in healthy individuals. We hypothesize that similar structural enhancements could be observed in post-stroke individuals after ET.

In our recent study, we demonstrated that the paretic muscles exhibited greater stiffness in comparison to the healthy muscles and the highest stiffness was predominantly observed in the GM, especially in the distal region at 20° (42). These observations prompt considerations regarding the potential relevance of eccentric exercise in the context of paretic muscle. In fact, eccentric exercise involves active stretching of the muscle, thereby engaging both the contractile and elastic components of the skeletal muscle. Notably, studies involving ultrasound imaging in healthy individuals have shown that this type of training can induce a reduction in passive muscle stiffness (43, 44), an increase in fascicle length, and muscle thickness (45, 46). These adaptations are likely the result of an increase in the number of sarcomeres in series and in parallel (47). Such muscle adaptations contribute to enhanced muscular strength, particularly at greater muscle lengths (48), by improving the tension-length relationship of the muscle (48, 49). Moreover, ET, which involves lengthening the muscle while producing force, is particularly effective in the context of stroke rehabilitation. It can increase force production, reduce muscle stiffness, and consequently improve the overall function of the muscle-tendon complex and functional capacity (45, 50, 51). However, to the best of our knowledge, no studies have thoroughly examined the potential modifications or improvements in the biomechanical properties of the paretic muscle following eccentric exercise. This gap in research limits our ability to draw conclusive insights into the potential enhancements or lack thereof in addressing the inherent issues associated with spastic paresis.

Walking performance is influenced by lower-extremity muscle strength (28). Particularly, the PF are pivotal in the walking process, serving as agonists and contributing to concentric activity that significantly impacts the quality of propulsion during walking (52). However, the effect of ET interventions on walking function in individuals with spastic paresis has produced mixed results in prior studies. While some investigations have reported significant improvements in walking speed and function (53, 54), others have not observed significant enhancements (55). This variability in outcomes may be attributed to the timing of intervention, as some studies were conducted during the chronic phase, typically after six months post-injury, when spasticity may have become fully established. This study seeks to address this potential limitation by implementing the intervention during the sub-acute phase. Furthermore, other factors such as the intensity of eccentric exercise, its duration, and the overall methodology of intervention may also play a role in these divergent findings, warranting further investigation.

## Limitations

4

One notable limitation of this study is the heterogeneity within the stroke patient population. Even though participants are in the sub-acute phase, the variability in individual recovery trajectories, severity of stroke, and pre-existing health conditions could lead to significant differences in response to the interventions. This heterogeneity may influence the outcomes and interpretations, making it challenging to draw definitive conclusions that are broadly applicable to all sub-acute stroke patients. We aim to increase the sample size to minimize the effects of data heterogeneity and interpretation bias. Furthermore, this study will focus on penniform muscles. It has been suggested that SWV measurements with small deviations from the fiber direction, as determined by the probe-fascicle angle, may be potentially inaccurate (56). However, previous study on the GM have shown relatively reproducible stiffness measurements (57).

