### Randomization

2.3

The random assignment of participants to their respective groups will take place on the day they will be included in the study and will be supervised by the investigator. The randomization list will be created by an independent statistician from the clinical research unit. For the randomization process, a computer-generated list will be generated using the Clinical Trial Randomization Tool. This list will then be uploaded into an online case report form. Each study participant will be assigned a unique allocation study number in a sequential format (TMP00X). The rigorous blinding will be maintained until the database will be finalized. A blinded assessor will conduct three visits: one before, one in the middle, and one after the interventions, while unblinded kinesiologists, who provide treatment and exercise sessions, will not be involved in the assessment sessions. All required information stipulated by the study protocol will be entered diligently into the Electronic Data Capture system in real-time as it will be acquired.

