### Recruitment

2.4

Participants will be recruited from the clinic of Parc de Belleville in Paris between the 1st of January 2024 to 31st May 2024. Recruitment will be accomplished by disseminating study participation offers in clinical centers, and subsequently, the medical staff will compile a list of volunteers to the experimenter. To participate in this study, subjects will be invited for an admission consultation (Pre-inclusion) (J0) with the principal investigator. Before this consultation, the investigator will need to ensure that the patient meets the study’s inclusion and exclusion criteria.

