#### Inclusion criteria

2.4.1

- Adult aged 20 to 75 years.- Subacute hemiparesis (< 6 months).- BMI between 18.5 and 25.- Written consent to participate in the study.

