#### Exclusion criteria

2.4.2

- Ankle impairment- Botulinum toxin injections in PF within the last 4 months before study inclusion to ensure that the muscle properties were not influenced by the toxin’s effects.- Medical contraindication for maximal effort.- Neurodegenerative disorders.- Cardiovascular disorders.- History of epilepsy.

The investigator will explain the purpose of the study, and the experimental protocol. The patient will then be given time for consideration. If they will agree, on the day of admission, they will sign an informed written consent to participate in the study, and then they will undergo their initial evaluation (Ji).

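### A larger sample cannot remove bias, and the fixed unadjusted arm comparison leaves time since stroke unused at a cost in power

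*Protocol article*

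**What the plan says.** Section 4 (Limitations) names heterogeneity among stroke patients as a notable limitation even within the sub-acute phase, because "the variability in individual recovery trajectories, severity of stroke, and pre-existing health conditions could lead to significant differences in response to the interventions". Its response is: "We aim to increase the sample size to minimize the effects of data heterogeneity and interpretation bias". The article gives no sample size from which to increase and none to reach.

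The Discussion suggests that mixed results in earlier eccentric-training studies may come from when the intervention was given, and adds: "This study seeks to address this potential limitation by implementing the intervention during the sub-acute phase". Within this trial, time since stroke appears only as an entry limit in section 2.4.1: hemiparesis of less than six months, with no lower limit.

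Section 2.8 (Statistical methods) compares the arms by an independent t-test if the data are normal and by a Mann–Whitney U test otherwise. It names no covariate. On allocation, section 2.3 says that "a computer-generated list will be generated using the Clinical Trial Randomization Tool" and does not mention stratification either way.

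**The concern.** Two things in the text do not fit together.

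First, sample size is credited with reducing a bias. Bias of interpretation is not defined, but under any usual meaning it does not shrink as patients are added. A reader who accepts the sentence will trust a larger trial on a ground that sample size cannot supply.

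Second, the article says that timing and recovery course drive variation in outcome, then fixes a comparison that cannot use the one such variable it must already know for every patient. Whatever outcome variance time since stroke explains stays in the error term, and any chance difference between arms in time since stroke stays uncorrected. At stake is the precision of the comparisons of gait speed, range of motion, stiffness and strength.

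**Working it through.** The article states no sample size, effect, standard deviation (SD) or power, so there is no figure to reproduce. The figures below are illustrations. Assumptions not in the article: equal arms of n patients, two-sided 5% level, effects in units of the outcome SD, and time since stroke uniform on 0 to 6 months.

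**1. What a larger sample does.** The standard error (SE) of an arm difference is SD × √(2/n).
- n = 20: √(2/20) = 0.316 SD.
- n = 40: √(2/40) = 0.224 SD.

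The SD of time since stroke is 6/√12 = 1.73 months. The chance that arm means differ by more than 1 month is 2 × [1 − Φ(1/SE)], with SE = 1.73 × √(2/n).
- n = 10: SE 0.775, chance 19.7%.
- n = 20: SE 0.548, chance 6.8%.
- n = 40: SE 0.387, chance 1.0%.

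So a larger sample does lessen the effects of heterogeneity. The between-patient SD itself does not change.

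**2. What a larger sample does not do.** Suppose there is no true effect but a fixed bias of 0.2 SD (assumed). The rejection rate is Φ(b/SE − 1.96) + Φ(−b/SE − 1.96), with b = 0.2 and SE = √(2/n).

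| n per arm | Rejection rate |
|---|---|
| 20 | 9.7% |
| 40 | 14.5% |
| 80 | 24.4% |
| 160 | 43.2% |

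The bias stays at 0.2 SD while the test grows more certain of it. The article does not show that such a bias exists; the table shows only that sample size is no cure for one.

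**3. Is the unadjusted test valid?** Data were simulated with simple randomisation, an outcome correlated r = 0.3, 0.5 or 0.7 with time since stroke, n = 20 or 40, and 3,000 runs per setting. With no true effect, the t-test rejected in 4.7% to 5.3% of runs, and its mean estimate was within 0.01 SD of zero. It is unbiased and keeps its level.

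**4. What is lost.** If a covariate explains a share R² of the outcome variance, adjusting for it multiplies the required sample by 1 − R², so it is worth 1/(1 − R²) times the sample. For weeks since stroke alone, R² must be the share of the variance still unexplained after the outcome's own baseline value. The article gives no such figure; 10% to 30% is assumed.
- R² = 10%: 1/0.90 = 1.11.
- R² = 30%: 1/0.70 = 1.43.

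As an example, a 0.8 SD effect at 80% power needs 25 per arm by the normal approximation. With the covariate this becomes 25 × 0.90 = 22.5, so 23, or 25 × 0.70 = 17.5, so 18. In the simulation with 20 per arm and a 0.8 SD effect, power was about 0.69 to 0.70 unadjusted. Adjusted, it was 0.72 at r = 0.3 (R² = 9%) and 0.81 at r = 0.5 (R² = 25%).

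**The case against.** The strongest reply is that the sentence speaks of the effects of heterogeneity, not of heterogeneity itself, and that more patients do reduce those effects. This stands: step 1 confirms it, and only the bias half of the sentence is wrong. Nor is sample size the design's only answer. Eligibility narrows the population by time since stroke, age and BMI ("BMI between 18.5 and 25") and excludes conditions such as "Cardiovascular disorders". Randomisation guards against systematic imbalance, and the assessor is blinded. The Limitations text does, however, acknowledge the variation that remains within the sub-acute phase.

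A second reply is that leaving out a covariate is a question of efficiency, not an error. That also stands, and the point is put on those terms. It is still a point about this document, because section 2.8 names the tests instead of leaving the choice open.

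Some stronger readings are tempting but not supported:
- A reader might infer that allocation is unstratified and that the list should be regenerated. The article is silent on strata and blocks, which an article commonly leaves to the full protocol.
- A reader might infer that early patients improve faster whatever they receive, so that a chance imbalance could match a treatment effect. The article gives neither a recovery slope nor an effect size.
- A reader might infer from one clinic and five months of recruitment ("Participants will be recruited from the clinic of Parc de Belleville in Paris between the 1st of January 2024 to 31st May 2024") that no larger sample is possible. With no target and no accrual rate, this cannot be shown.
- A reader might want severity in the model as well. The outcome sections define no stroke-severity measure.

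**Conclusion.** The point holds in two limited parts. The claim that a larger sample minimises bias is wrong and, with no number attached, the proposed increase has no content that can be checked. The fixed arm comparison also leaves out a prognostic candidate that the article's own reasoning singles out and that screening must establish.

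The consequence is lost power and precision, not an invalid test or a biased estimate. Its size rests on the assumed 10% to 30% of remaining variance, equivalent to about 1.1 to 1.4 times the sample. If weeks since stroke add little once the baseline outcome value is known, the gain will be near the lower end or below it.

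**What to change.** In section 4, delete the statement that a larger sample will minimise bias; a statement about precision may stay. In section 2.8, replace the unadjusted between-arm test with a linear model of the final value on arm, baseline value of the same outcome and weeks since stroke. Fix the model before unblinding, and specify a rank-based or robust version for outcomes whose residuals are clearly non-normal. Record time since stroke as a number of weeks, not only as meeting the limit. Add a baseline severity measure only if one is already collected, and include any factor by which the list was in fact stratified.

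The cost is about one degree of freedom per covariate and a little more analysis work. It needs no extra patients or visits and no change to the randomisation list.

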## Conclusion

5

This study protocol proposes an innovative comparison between ET and conventional therapy for improving outcomes in post-stroke survivors during the sub-acute phase. Preliminary evidence supports ET’s potential to enhance structural, neuromuscular, biomechanical, and functional parameters, with notable improvements expected in muscle strength, stiffness, and walking performance. However, existing research has yet to fully elucidate the specific biomechanical adaptations in paretic muscles following ET, highlighting a significant gap in our understanding. This study aims to address this gap, offering new insights into stroke rehabilitation practices. The outcomes of this research could inform future clinical approaches, emphasizing the critical need for high-quality, targeted interventions in the early stages of stroke recovery.
